#### Primary outcome measures

The primary outcome was measured using the visual analogue scale (VAS) for bothersomeness of low back pain. Since our intension was not to simply evaluate the severity of pain, but also to understand the impact of chronic low back pain on the patients' life, we used the VAS not for pain intensity, but for bothersomeness of low back pain, as a primary outcome measurement. The patient was asked to mark, on a 10-cm VAS (0, absence of bothersomeness; 10, the worst bothersomeness imaginable), the degree of bothersomeness due to low back pain experienced within the most recent one week from the day the assessment was performed. This measurement has substantial validity; it is highly correlated with measures of function and other outcome measures[13]. Bothersomeness of low back pain was measured at baseline, and on the 4, 6, 8, 12, and 24-week follow-ups. The primary endpoint was the 8 week follow-up, i.e. 2 weeks after completion of the 10-12 sessions of acupuncture treatment.

#### Secondary outcome measures

There is ample evidence supporting the validity of the visual analogue scale (VAS) for pain intensity. Many studies have demonstrated the validity of its construct and its reliability [14,15]. This is a fast and straightforward method for evaluating the subjective intensity of pain. Pain intensity was measured in the same fashion as VAS for bothersomeness (0, absence of pain; 10, the worst pain imaginable) at baseline, 4, 6, 8, 12 and 24 weeks after beginning of treatment.

The Oswestry Disability Index (ODI) [16] was used to measure back pain-related dysfunction. ODI includes 10 questions about daily activities including pain intensity, personal care, lifting, walking, sitting, standing, sleeping, sexual life, social life, and traveling. Each question is rated on a 0 to 5 point scale and the lower the score, the less disabled. It takes 5 minutes to complete and the validated Korean version of ODI [17] was administered at baseline, 6, 8, 12, and 24-week follow-ups.

Health-related quality of life was measured at baseline, and at 6, 8, 12, and 24-week follow-ups, using the well-validated SF-36 [18], which has been recommended for back pain studies. The SF-36 measures 8 health domains: 1) limitations in physical activity because of health problem; 2) limitations in social activities because of physical or emotional problem; 3) limitations in usual role activities because of physical health problems; 4) bodily pain; 5) general mental health (psychological distress and well-being); 6) limitations in usual activities because of emotional problems; 7) vitality (energy and fatigue); and 8) general health perceptions. The higher score means better general health status. In our study, the validated Korean version of SF-36 [19] was analyzed.

Patients completed the EuroQol 5-Dimension (EQ-5D) [20] at baseline, and at the 6, 8, 12 and 24-week follow-ups. EQ-5D is a generic questionnaire that measures the quality of life regarding personal health. It consists of two parts: in the first part, the patient evaluates in a descriptive way his/her health state, with respect to 5 dimensions, namely mobility, personal care, daily activities, pain/discomfort and anxiety/depression. Each dimension is scored from one to three, and so the best possible health profile is 11111 and the worst is 33333. In the second part, the patient rates on a VAS from 0, the worst imaginable state of health to 100, the best imaginable state of health, his/her overall state of health on the day the questionnaire is completed. The two scores are complementary. EQ-5D has an index of reference value of possible health profiles ranging from a value of one (the best state of health) to zero (death). Thus, we sought to combine these results with the years of life in order to calculate the years of life adjusted for health-related quality of life. Using this approach, as well as analyzing cost-effectiveness, we performed a cost-utility analysis. A validated Korean version of EQ-5D [21] was administered in this study.

The Korean version of Beck's Depression Inventory (BDI) [22] is a 21-item self-administered questionnaire. It provides a quantitative measure of depressive symptoms. Each item has a 0-3 response format, giving a theoretical maximum score of 63. The following cut-off scores are recommended: scores 0-9 little, if any, depression, 10-18 mild depression, 19-29 moderate depression, and 30-63 severe depression. The psychometric quality of the questionnaire is very good [23]. The validated Korean version of the credibility test, which was first proposed by Vincent [24], was used to assess the credibility of real and sham acupuncture treatments at the end of the 6-week treatment. The patients rated the credibility of the treatment they were given by answering 4 questions on a numeric rating scale, with 0 for not at all and 6 for maximal agreement: 1) improvement expected; 2) recommendation to others; 3) treatment logical; and 4) effective also for other diseases.

### Protection of subjects and assessment of safety

Any adverse experiences at any clinic visit during the 12 sessions were monitored. The research team monitored serious adverse experiences, which were defined as treatment-related experiences.

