### Outcome measurements

Patient completed a series of measurements to assess back pain-related dysfunction, pain, quality of life, and back pain-related costs.

At the screening visit, patients were asked to fill out a questionnaire regarding age, gender, marital status, residence, occupation, and education. Medical history was also taken before physical check-ups and it was determined whether the patient would be included or not. The baseline (T0), 4 (T1), 6 (T2), 8 (T3), 12 (T4), and 24 (T5) week follow-up measurements are summarized in Table 1.

**Table 1 T1:** Schedule for data collection; outcome measures per visits

Measures	Baseline (0-week)	4-week	End of treatment (6-week)	8-week	12-week	24-week
Sociodemographic characteristics	X					
Back pain history	X					
X-ray	X			X		
VAS for bothersomeness of low back pain	X	X	X	X	X	X
VAS for pain intensity	X	X	X	X	X	X
Oswestry disability Index (ODI)	X		X	X	X	X
General health status (SF-36)	X		X	X	X	X
EuroQol-5D (EQ-5D)	X		X	X	X	X
Beck Depression Inventory (BDI)	X		X	X	X	X
Medication use	X		X	X		
Costs of back care	X		X	X		X
Adverse experiences*	X	X	X			
Credibility test†	X		X			
Acupuncture experience (In-depth interview)§				X		

*, At every single visit; †, After 1st treatment and at the end of treatment (6-week); §, 10 randomly chosen participants (5 from acupuncture group and 5 from sham group) for each hospital, thus 30 in total.

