### Stopping rules

The trial would have been stopped if the principle investigator believed there was an unacceptable risk of serious adverse events in one of more of the treatment arms.

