### Sample size determination

Generally, a level of significance of α = 0.05 and a power of 1-ß = 0.80 were used. For two arms (control - sham acupuncture, experimental - real acupuncture), we considered the two sample t-test model.

Experimental group: real acupuncture

Control group: sham acupuncture

Primary parameter: VAS for bothersomeness at 2 months after beginning of treatment

Expected mean difference and common standard deviation between two groups: 1.5 on a 0-10 VAS for bothersomeness, SD = 2.73

Drop-out rate: 20%

Sample size determination:(1)

where,

*N *: total sample size

*n*_*t *_: sample size for experimental group

*n*_*c *_: sample size for control group

r: number of experimental group

s: number of control group

λ: ratio of experimental and control sample size (λ = *n*_*t*_/*n*_*c*_)

In the trial, r = 1, s = 1 and λ = 1 were assumed, and then *N *= *n*_*t *_+ *n*_*c *_

To determine optimal sample size, we considered the following hypotheses of interest and formulas of sample size

Under hypotheses *H*_0_: μ_c _= μ_t _*H*_1_: μ_c _≠ μ_t _

sample size:(2)

μ_t _: mean of experimental group

μ_c _: mean of control group

σ^2 ^: common variance between two groups

α: probability of type 1 error (significance level)

ß: probability of type 2 error

Z_α/2_: α/2th quantile of standard normal distribution

Z_ß _: ßth quantile of standard normal distribution(3)

μ_c_-μ_t _= 1.5, σ = 2.73(Reference: Cherkin et al)[25]

Using formulas (1) above:(4)

For the equal allocation for the two groups, total sample size considering drop-out rate of 20% was calculated as 130 subjects.

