#### Safety

All adverse effects were recorded and described as frequency and percentage. For the comparison of adverse effects between groups, the Chi-square test or Fisher's exact test were performed.

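### Serious adverse experiences are defined by treatment-relatedness, which confuses seriousness with causality, and the stopping judgement has no other definition of serious to rest on

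*Protocol article*

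**What the plan says.** The section Protection of subjects and assessment of safety has two sentences. The first sets general monitoring, with no restriction on cause: "Any adverse experiences at any clinic visit during the 12 sessions were monitored". The second gives the only definition of serious in the article: "The research team monitored serious adverse experiences, which were defined as treatment-related experiences". No criterion of outcome or severity accompanies it.

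The Stopping rules section makes stopping depend on whether the principal investigator "believed there was an unacceptable risk of serious adverse events in one of more of the treatment arms". It gives no count, rate or threshold.

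The Safety paragraph of the statistical methods says: "All adverse effects were recorded and described as frequency and percentage". For the comparison between groups, "the Chi-square test or Fisher's exact test were performed". It does not mention a serious category.

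In Table 1 (Outcome measurements), the adverse-experiences row is ticked at baseline, 4 weeks and 6 weeks. The footnote to that row reads "At every single visit".

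**The concern.** Seriousness describes what happened to the patient. Relatedness describes what is thought to have caused it. They are separate attributes, and a safety record needs both. When one is defined as the other, the serious category no longer shows how often serious events occurred in each arm. It shows how often events were attributed to treatment.

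This is not a detail that a condensed article leaves to the full protocol. The article states a definition, and the definition is wrong as stated.

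Two things are at stake. A reader of the results could not interpret a reported number of serious events. And the single stopping criterion uses the word serious with no other meaning supplied.

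The collection window is a separate matter. Participants are assessed up to 24 weeks, and the article is not consistent on whether adverse experiences are sought after week 6.

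**Working it through.** **The plan's own figure.** The only design figure is the total of 130, and it does not depend on this point. Inputs from Sample size determination: difference 1.5, SD 2.73, two-sided α 0.05, power 0.80, drop-out 20%, equal allocation.

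- Per arm: 2 × (1.96 + 0.8416)² × 2.73² / 1.5² = 2 × 7.849 × 7.4529 / 2.25 = 52.0, so 52.
- After drop-out: 52 / 0.80 = 65 per arm, 130 in total.

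The figure reproduces, and changing the definition of serious leaves it as it is.

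**Step 1: the definition.** Every event falls into one of four combinations. The table compares the literal wording, a charitable reading (the authors meant events that were serious and also treatment-related), and a definition by outcome.

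| Outcome of event | Judged related? | Literal wording | Charitable reading | Defined by outcome |
|---|---|---|---|---|
| Serious (e.g. hospitalisation) | Yes | Serious | Serious | Serious |
| Serious (e.g. hospitalisation) | No | Not serious | Not serious | Serious |
| Minor (e.g. needle-site bruise) | Yes | Serious | Not serious | Not serious |
| Minor (e.g. needle-site bruise) | No | Not serious | Not serious | Not serious |

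The literal wording misclassifies two of the four combinations and the charitable reading one. The serious event judged unrelated is misclassified under both.

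**Step 2: what happens to that event.** General monitoring covers adverse experiences of any cause at clinic visits during treatment, and the Safety paragraph tabulates all adverse effects. A hospitalisation judged unrelated and reported in that period can therefore be recorded. What it loses is the serious label. One doubt remains: adverse effects could be read as related events only, and the text does not settle this.

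**Step 3: the stopping rule.** It speaks of serious adverse events, whereas the safety section defines serious adverse experiences. The terms differ, but no other definition is offered, so the natural reading carries the faulty one across. The link is plausible but not stated.

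**Step 4: the collection window.** Scheduled post-baseline assessments are at 4, 6, 8, 12 and 24 weeks, five in all.

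- The safety section limits monitoring to the treatment sessions, that is, 6 weeks.
- The Table 1 ticks agree: baseline, 4 and 6 weeks. Three of the five post-baseline assessments (8, 12 and 24 weeks) are unticked, and they span the remaining 24 − 6 = 18 weeks.
- The Table 1 footnote says every visit. If it means treatment visits, it agrees with the ticks and there is no marked collection after week 6. If it means every assessment, it contradicts both the ticks and the safety section.

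**The case against.** The strongest defence is that the sentence is loosely compressed and was meant to say that serious events attributable to treatment were watched closely. On that reading the bruise example falls away. The exclusion of serious events judged unrelated does not, so the defect survives in its more important half.

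A second defence is that general recording of adverse experiences continues and that efficacy is untouched. Both parts stand. They limit the harm but do not make the definition right.

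A reader might also infer four stronger things, which the article does not support:

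- **That serious events judged unrelated go uncounted.** General monitoring during treatment has no causal filter, so such events may be recorded but are not labelled serious.
- **That the stopping rule relies on a count of these events.** It rests on the principal investigator's belief about risk, and no count is mentioned.
- **That the between-arm safety comparison is built on the serious category.** The Safety paragraph compares adverse effects in general.
- **That relatedness is judged by people who know the arm.** Practitioners must know which device they use, but no section says who judges relatedness. The Overview says outcome assessment was blinded, without saying whether that covers adverse events.

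Nor can one say that adverse events are certainly not collected after week 6, because the Table 1 footnote leaves it open.

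**Conclusion.** The point holds for the definition. The article makes causality the test of seriousness, which is wrong as written, and its only stopping criterion uses serious with no other definition. Misclassification affects two of four combinations read literally and one read charitably. The number of participants affected cannot be estimated, because the article gives no event rates. The primary endpoint, the sample size of 130 and the efficacy analysis are unaffected.

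The conclusion rests on one assumption: that the stopping rule's serious adverse events are the safety section's serious adverse experiences. If a different definition applies there, the article should give it.

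The collection window is an inconsistency to reconcile and is not evidence that collection stopped. It does not add weight to the point about the definition.

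**What to change.** 1. Replace the definition with one based on the outcome of the event regardless of cause: death, life-threatening event, hospitalisation, lasting disability, or another medically important event.
2. Record relatedness in a separate field of the case report form, and state who judges it.
3. Tabulate serious events by arm, both overall and by relatedness, alongside the planned table of all adverse effects.
4. Use the same term and the same definition in the stopping rule.
5. Reconcile the safety section, the Table 1 ticks and the Table 1 footnote on when adverse experiences are collected. If collection does end at 6 weeks, add the adverse-event question to the 8-, 12- and 24-week assessments.

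The cost is one sentence of definition, one form field, one extra table and, if needed, one question at assessments that already take place. If data collection is complete, the recorded events can be reclassified by outcome as far as the forms allow, and the report should state the collection window actually used.

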### Stopping rules

The trial would have been stopped if the principle investigator believed there was an unacceptable risk of serious adverse events in one of more of the treatment arms.

### Sample size determination

Generally, a level of significance of α = 0.05 and a power of 1-ß = 0.80 were used. For two arms (control - sham acupuncture, experimental - real acupuncture), we considered the two sample t-test model.

Experimental group: real acupuncture

Control group: sham acupuncture

Primary parameter: VAS for bothersomeness at 2 months after beginning of treatment

Expected mean difference and common standard deviation between two groups: 1.5 on a 0-10 VAS for bothersomeness, SD = 2.73

Drop-out rate: 20%

Sample size determination:(1)

where,

*N *: total sample size

*n*_*t *_: sample size for experimental group

*n*_*c *_: sample size for control group

r: number of experimental group

s: number of control group

λ: ratio of experimental and control sample size (λ = *n*_*t*_/*n*_*c*_)

In the trial, r = 1, s = 1 and λ = 1 were assumed, and then *N *= *n*_*t *_+ *n*_*c *_

To determine optimal sample size, we considered the following hypotheses of interest and formulas of sample size

Under hypotheses *H*_0_: μ_c _= μ_t _*H*_1_: μ_c _≠ μ_t _

sample size:(2)

μ_t _: mean of experimental group

μ_c _: mean of control group

σ^2 ^: common variance between two groups

α: probability of type 1 error (significance level)

ß: probability of type 2 error

Z_α/2_: α/2th quantile of standard normal distribution

Z_ß _: ßth quantile of standard normal distribution(3)

μ_c_-μ_t _= 1.5, σ = 2.73(Reference: Cherkin et al)[25]

Using formulas (1) above:(4)

For the equal allocation for the two groups, total sample size considering drop-out rate of 20% was calculated as 130 subjects.

### Statistical methods and analysis

All statistical analysis was performed in the principle of ITT analysis (Intention-To-Treat analysis) and PP analysis (Per-Protocol analysis). In the case of ITT analysis, we applied the LOCF (Last Observation Carried Forward Analysis) rule. For all statistical analysis, SPSS Win. Ver.14.0 and a significance level of 0.05 were used.

#### Description of baseline characteristic and homogeneity test of two groups

For the description of baseline characteristics, both demographical and clinical, for all subjects in the clinical trial, the mean with standard deviation, range with minimum and maximum for quantitative data and frequency with percentage for qualitative data are described.

For the homogeneity test of the baseline characteristics, both demographical and clinical, between the two groups, two-sample t-test for quantitative data and Chi-square test for qualitative data were performed. If there were baseline characteristics showing statistical significance and possibility of covariance, ANCOVA (analysis of covariance) was used for analysis and adjustment of baseline characteristics.

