#### Efficacy

##### • Primary variable

The two-sample T-test was used for VAS for bothersomeness of low back pain at baseline and at 8 weeks for the comparison of the two groups and to determine differences from baseline. ANCOVA and two-sample T-test was used between the differences at baseline VAS and 8 week VAS for each groups. Also, a 95% confidence interval was added for all analyses.

Repeated measure two factor analysis will be used to analyze the difference and mean change among baseline, and 4, 6, 8, 12 and 24-week VAS, difference and mean change between groups, and interaction between groups and observed time. If necessary, a mixed model approach was also used.

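### The protocol contradicts itself on whether baseline adjustment of the primary outcome depends on a baseline significance test, and names neither the covariate nor the primary analysis

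*Protocol article*

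**What the plan says.** The protocol article deals with adjustment in two places.

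- **Description of baseline characteristic and homogeneity test of two groups.** The arms are compared on demographic and clinical baseline variables: "two-sample t-test for quantitative data and Chi-square test for qualitative data were performed". The result decides the adjustment: "If there were baseline characteristics showing statistical significance and possibility of covariance, ANCOVA (analysis of covariance) was used". Two conditions must hold, a significant difference and a possible covariance. The second is not defined.
- **Efficacy, Primary variable.** The first sentence gives "The two-sample T-test was used for VAS for bothersomeness of low back pain at baseline and at 8 weeks", covering the comparison of groups and the differences from baseline. The next sentence adds "ANCOVA and two-sample T-test was used between the differences at baseline VAS and 8 week VAS for each groups". No condition is attached to this ANCOVA and no covariate is named. A repeated-measures analysis over all visits follows. None of these is designated as the primary analysis.

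The sample size section rests on an unadjusted comparison: "we considered the two sample t-test model", with "1.5 on a 0-10 VAS for bothersomeness, SD = 2.73".

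**The concern.** In a randomised trial, a baseline difference between arms that arises from the allocation is chance. Its p-value says nothing about whether the variable predicts outcome, and prediction is the reason to adjust. A prognostic variable that differs at p = 0.10 fails the first condition and is left out, however strong it is. The covariates are also settled only after the arms have been compared, so the model depends on the data.

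The variable that matters most here is baseline bothersomeness VAS, which is measured in everyone. One section makes its use conditional on significance; the other lists ANCOVA without a condition. Two analysts could follow the article faithfully and report different primary models. At stake are precision that costs nothing to obtain and a primary result that does not depend on which sentence is followed.

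**Working it through.** **Inputs from the article (Sample size determination):** difference 1.5, SD 2.73, "a level of significance of α = 0.05 and a power of 1-ß = 0.80 were used", a two-sided test ("α/2th quantile of standard normal distribution"), 1:1 allocation, 20% drop-out, total 130.

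**Assumption:** the correlation r between baseline and week-8 VAS is not given, so it is shown over a range.

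**Step 1. Reproduce the plan's figure.** n per arm = 2 × [2.73 × (1.960 + 0.842) / 1.5]² = 51.997, rounded up to 52. Then 52 / 0.80 = 65 per arm, or 130 in total. This matches exactly. The target is 52 completers per arm for an unadjusted t-test: power is 0.800 by the normal formula and 0.793 by the noncentral t.

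**Step 2. How often the trigger fires.** Under randomisation, a 5% test of baseline VAS is significant in about 5% of trials (4.8% to 5.3% in simulation). If the trigger governs, baseline VAS is left out in about 95% of trials.

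**Step 3. Power of three possible primary analyses, 52 per arm.**
- ANCOVA on baseline VAS in every case: residual SD = 2.73 × √(1 − r²), power by the noncentral t.
- Triggered rule: ANCOVA if baseline VAS differs at p < 0.05, otherwise the week-8 t-test; 20,000 simulated trials.
- Change-score t-test: SD = 2.73 × √(2(1 − r)), assuming equal SD at both times.

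| r | ANCOVA SD | ANCOVA always | Triggered rule | Change-score SD | Change score |
|---|---|---|---|---|---|
| 0.3 | 2.60 | 0.829 | 0.80 | 3.23 | 0.65 |
| 0.4 | 2.50 | 0.857 | 0.80 | 2.99 | 0.72 |
| 0.5 | 2.36 | 0.893 | 0.81 | 2.73 | 0.79 |

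ANCOVA in every case therefore gains about 3, 6 and 9 points over the triggered rule. Over this range the change score does no better than the unadjusted week-8 test, because it fixes the baseline slope at 1.

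**Step 4. Type I error of the triggered rule.** Simulated size is about 4.8% at r = 0.3 and 4.4% at r = 0.5, slightly below the nominal 5%.

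**Step 5. Imbalance left uncorrected just below the trigger.** The largest non-significant baseline difference is 1.98 × 2.73 × √(2/52) = 1.06 points, again with equal SD at both times. It moves the unadjusted week-8 difference by r × 1.06 = 0.32, 0.42 and 0.53 points, which is 21%, 28% and 35% of the 1.5-point target. This is conditional on such an imbalance; over repeated randomisations the unadjusted estimate is unbiased.

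**Step 6. The other reading.** If the ANCOVA in the primary-variable section uses baseline VAS and is the primary analysis, the ANCOVA column applies and the loss is zero.

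**The case against.** The strongest reply is that the section defining the primary analysis lists ANCOVA unconditionally. A reader of the baseline section alone might infer that baseline VAS would be omitted in 95% of trials. The article as a whole does not support that, because the figure holds only if the trigger also governs the primary variable. The change-score and repeated-measures analyses also use the baseline value. This reply stands, and it limits the point. It does not settle the matter: no covariate is named, no analysis is designated primary, the only statement of when ANCOVA applies is the conditional one, and the trial is sized on the unadjusted test.

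Other tempting inferences also fail.
- That an irrelevant variable at p = 0.03 would be adjusted for: the second condition, though undefined, is naturally read as requiring a relation to outcome.
- That the choice of model is made unblinded: the Overview says the statistical analysis was done by people blinded to assignment, and a baseline comparison needs only coded arms.

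The gain may also be modest. Entry requires a screening VAS of at least 5, which restricts the baseline range and would tend to lower r. With LOCF under ITT, up to 65 per arm are analysed. Ignoring any dilution from carrying values forward, unadjusted power is then 0.875 and ANCOVA at r = 0.3 gives 0.903, a gain of about 3 points. This bears on the size of the gain and does not justify the trigger.

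**Conclusion.** The point holds as an internal conflict and a poorly chosen rule. The article states both a conditional and an unconditional use of ANCOVA, leaves the covariate unnamed and designates no primary analysis. If the trigger governs, the cost relative to adjusting in every case is about 3 to 9 points of power at assumed correlations of 0.3 to 0.5, with 52 per arm. If the unconditional ANCOVA on baseline VAS is primary, the cost is zero.

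A reader might go further and conclude that the trial is underpowered, biased or prone to false positives. The figures do not support that. The planned 80% rests on an unadjusted t-test and is still met, randomisation keeps the estimate unbiased on average, and the triggered rule is slightly conservative. The harm is forgone precision and a data-dependent, unsettled primary model. Severity: should fix.

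**What to change.** - Remove baseline significance as the trigger for adjustment and keep the baseline table descriptive.
- Name one primary analysis before outcomes are compared by arm: ANCOVA of week-8 bothersomeness VAS on treatment arm, adjusted for baseline VAS and for centre, since randomisation was done per centre. Report the adjusted difference with its 95% confidence interval.
- Label the week-8 t-test, the change-score t-test and the repeated-measures analysis as supportive.
- Adjust each secondary score for its own baseline value.

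The cost is about one paragraph of analysis wording. No extra data, visits or participants are needed, because baseline VAS and centre are already recorded for everyone. The sample size of 130 can stay as it is.
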